# Tailored interventions to implement recommendations for elderly patients with depression in primary care: a study protocol for a pragmatic cluster randomised controlled trial

**DOI:** 10.1186/1745-6215-15-16

**Published:** 2014-01-09

**Keywords:** Depression, Elderly, Primary care, Tailored interventions, Implementation science, Cluster randomised trial

## Abstract

**Background:**

The prevalence of depression is high and the elderly have an increased risk of developing chronic course. International data suggest that depression in the elderly is under-recognised, the latency before clinicians provide a treatment plan is longer and elderly patients with depression are not offered psychotherapy to the same degree as younger patients. Although recommendations for the treatment of elderly patients with depression exist, health-care professionals adhere to these recommendations to a limited degree only. We conducted a systematic review to identify recommendations for managing depression in the elderly and prioritised six recommendations. We identified and prioritised the determinants of practice related to the implementation of these recommendations in primary care, and subsequently discussed and prioritised interventions to address the identified determinants. The objective of this study is to evaluate the effectiveness of these tailored interventions for the six recommendations for the management of elderly patients with depression in primary care.

**Methods/design:**

We will conduct a pragmatic cluster randomised trial comparing the implementation of the six recommendations using tailored interventions with usual care. We will randomise 80 municipalities into one of two groups: an intervention group, to which we will deliver tailored interventions to implement the six recommendations, and a control group, to which we will not deliver any intervention. We will randomise municipalities rather than patients, individual clinicians or practices, because we will deliver the intervention for the first three recommendations at the municipal level and we want to minimise the risk of contamination across GP practices for the other three recommendations. The primary outcome is the proportion of actions taken by GPs that are consistent with the recommendations.

**Discussion:**

This trial will investigate whether a tailored implementation approach is an effective strategy for improving collaborative care in the municipalities and health-care professionals’ practice towards elderly patients with depression in primary care. The effectiveness evaluation described in this protocol will be accompanied with a process evaluation exploring why and how the interventions were effective or ineffective.

**Trial registration:**

ClinicalTrials.gov: NCT01913236

## Background

The prevalence of depression in the elderly is high [1,2] and increases with age, even within the elderly [3-5]. Elderly patients with depression are to a large extent treated in primary health care, and they prefer to be treated by their general practitioner [6,7]. The risk that an elderly patient with depression develops a chronic episode is estimated to be approximately 30% [8,9]. Depression in the elderly has a negative impact on quality of life, the episodes of the disease are longer, and the risks of hospitalisation and mortality are increased [10]. Medical co-morbidities, which increase with advancing age, have a negative effect on treatment response and prognosis [10,11]. Practitioners’ attitudes towards and experience with depressed elderly patients affect the probability of providing a patient with an adequate treatment strategy [12], and patients’ attitudes and beliefs towards the treatments might affect adherence and outcomes [13,14]. Elderly patients with depression are less likely to be offered a course of psychotherapy [15], and GPs’ latency before reaching a decision with regard to a treatment strategy is longer. In Norway elderly patients are not referred to district psychiatric centres to the same degree as younger adults and when referred, the duration of contact for the treatment is shorter [16]. To our knowledge, psychiatrists and psychologists in private practice treat elderly patients with depression to a very limited degree only. International studies indicate that general practitioners accurately diagnose about 50% of patients with depression [17], and approximately 40% of practice is in accordance with depression guidelines [18].

As there was no clinical practice guideline for managing depression in the elderly in Norway, and only a national guideline on the management of depression among adults in general, we conducted a systematic review, assessing 13 national and international clinical practice guidelines for managing depression in primary care [19]. We identified all relevant recommendations for elderly patients with depression. We prioritised six of these recommendations for implementation.

### The six prioritised recommendations for managing depressed elderly patients

#### Social contact

Primary-care physicians and other health-care professionals should discuss social contact with elderly patients with depression, and recommend actions (for example, group activities) for those who have limited social contact. When needed, regular social contact should be provided with trained volunteers recruited from Centres for Voluntary Organisations, the Red Cross, Mental Health or community day care centres. When possible, the patient’s relatives should be involved in the plan to improve social contact.

#### Collaborative care

All municipalities should develop a plan for collaborative care for patients with moderate to severe depression. The plan should describe the responsibilities and communication between professionals who have contact with the patient, within primary care and between primary and specialist care. In addition, the plan should appoint depression care managers who have a responsibility for following the patient. The plan should describe routines for referral to specialist care. Municipalities are the atomic unit of local government in Norway and are responsible for outpatient health-care services, senior citizen services and other social services. There are 428 municipalities.

#### Depression care manager

Primary-care physicians should offer patients with moderate to severe depression regular contact with a depression care manager.

#### Counselling

Primary-care physicians or qualified health-care professionals should offer advice to elderly patients with depression regarding:

• Self-assisted programs, such as literature or web-based programs based on cognitive behavioural therapy (CBT)

• Structured physical activity programmes, individually or group based

• Healthy sleeping habits

• Strategies for coping with anxiety

• Problem-solving

#### Mild depression

Primary-care physicians should not prescribe antidepressants to patients with mild depression. Primary-care physicians may consider prescribing antidepressant medication to patients who suffer from a mild episode of depression and have previously responded to antidepressants when moderately or severely depressed.

#### Severe depression, recurrent depression, chronic depression and dysthymia

Primary-care physicians should offer these patients a combination of antidepressant medication and psychotherapy. If the physician is not trained to provide the patient with psychotherapy, patients should be referred to trained health-care professionals.

### Usual care

The following description of usual care for depression management in the elderly in Norway is based on clinical experience, government reports and scientific publications. We have also included international data, if data specific for Norwegian practice are lacking. We describe usual care with regard to the six prioritised recommendations.

#### Social contact

Isolation and loneliness are major risk factors for developing depression [20]. Although Norway has a scattered population, 44% live in one of the six largest city areas [21]. The proportion of elderly is higher in the rural areas. The recommendation addresses several levels of the municipality, from primary health-care providers (physicians, nurses and occupational therapists) and voluntary organisations. Some municipalities have included voluntary organisations and volunteers in their health-care planning, whereas others have no such collaboration. To some extent volunteers are involved in the follow-up of psychiatric patients of all ages. We believe that primary-care practitioners in general have neither routines nor procedures for involving volunteers in the management of elderly patients with depression.

#### Collaborative care

Although some municipalities and city districts have developed a general plan for managing patients with mental-health-related disorders, we believe that this is not the rule for most. A specific plan for depression care management is, at best, a part of such a plan. Specific plans for managing elderly patients with depression are absent. Many health-care regions have signed agreements on collaboration between the municipality and specialist health-care services. These statements are merely advisory, and do not dictate health-care providers’ behaviour.

#### Depression case manager

A Norwegian-register-based study found that approximately 1/3 of patients did not get a repeat prescription for antidepressants [22]. This may indicate that a more thorough follow-up, by a depression case manager, might improve the patients’ adherence to the treatment plan. The evidence for this service as part of a collaborative care plan is substantial [23,24], but has, to our knowledge, not been implemented or evaluated systematically in Norway. The service is intended to be an addition to the GP’s follow-up plan. Municipalities in Norway have developed community psychiatric nurse services to a large degree. These services do not serve all patients who need such care, and, when limited, we believe that elderly patients with depression are not prioritised in the community.

#### Counselling

This recommendation addresses several aspects of depression care management. The recommendation is addressed to health-care professionals. It is primarily relevant to GPs, but also to specially trained nurses. In addition, some sort of coordination with voluntary organisations or enterprises that offer physical training or activity programmes is needed. We believe that the actions in this recommendation are frequently used by practitioners, albeit not in a systematic or coordinated way. Evidence-based tools for providing advice on self-help, sleep problems, anxiety and problem-solving therapy will be identified and disseminated. Health-care professionals need to be trained for some of the actions, particularly problem-solving therapy and coping strategies. We believe that approximately 10% of GPs have some formal training in cognitive behavioural therapy, which also is useful.

#### Mild depression

This recommendation is addressed to GPs. We believe that current practice is characterised by prescribing antidepressants as soon as a diagnosis of depression is established, regardless of depression severity.

#### Severe depression, recurrent depression, chronic depression and dysthymia

This recommendation addresses primary-care professionals, primarily GPs and community psychiatric nurses, but also psychiatrists and psychologists in private practice and community psychiatric centres and geriatric psychiatric services, which are organised within the specialist health-care system. We believe that elderly patients with chronic or recurrent depression may be referred to and, to some extent, followed up by specialists, primarily in outpatient clinics of geriatric psychiatry and to a lesser extent in community psychiatric centres [16]. Elderly patients with these forms of depressive disorder are offered therapy by psychologists and psychiatrists in private practice to a very limited degree [22]. Most of these patients are offered pharmacotherapy, but they do not receive adequate psychotherapy.

### Tailored implementation

Tailored interventions are strategies that are designed to achieve changes in health-care practices based on an assessment of determinants of practice [25]. Determinants of practice are factors that can be barriers to or enablers of desired health-care practice. The factors that may affect practice are numerous, and can be found at all levels of the health-care system, including the organisational, professional and patient levels [26]. Within these levels, a variety of cognitive, emotional, economic and knowledge factors may affect the way health-care organisations and providers prioritise and provide services to patients and the way patients and their relatives adhere to the recommended care. Determinants of practice may vary across patient groups and settings. Thus, it is logical that determinants of practice should be identified in specific patient groups and health-care systems when recommendations for practice are implemented, and that the implementation interventions that are used should be tailored to address the identified determinants of practice. In the Tailored Implementation for Chronic Diseases (TICD) collaborative research project, we compared alternative methods for identifying determinants of practice and linking implementation strategies to identified determinants across countries and chronic diseases. The Norwegian component of the TICD project focuses on implementing recommendations for managing depressed elderly patients in primary care [27].

Although tailored interventions have been found to be effective, it is unclear how best to identify determinants of practice or how to tailor interventions to address the identified determinants [28]. In TICD, we developed a comprehensive checklist and worksheets to assist with the identification of determinants and tailoring of interventions [26]. The TICD checklist includes 57 items grouped in seven domains (guideline factors, individual health professional factors, patient factors, professional interactions, incentives and resources, capacity for organisational change and social, political and legal factors). We used the TICD checklist to identify key determinants of practice for each of the six prioritised recommendations for the management of depressed elderly patients. We used different methods to identify the determinants: brainstorming and structured focus groups with researchers, clinicians, nurses and patients; open and structured individual interviews with clinicians, nurses and patients, and a mailed survey of clinicians and nurses. Subsequently, we used different methods to identify and prioritise implementation strategies to address the key determinants that we had identified. These methods included independent assessments by the investigators informed by the TICD checklist, and unstructured and structured discussions in focus groups with clinicians, carers and other key stakeholders.

### Objectives

The objective of this study is to evaluate the effectiveness of tailored interventions to implement the six recommendations for the management of elderly patients with depression in primary care. The purpose of the trial is to inform decisions about how to improve care for depressed elderly patients in daily practice.

### Dissemination of results

The results of this study will be published in peer-reviewed journals and we will give oral and poster presentations at national and international conferences.

## Methods/design

### Trial design

We will conduct a pragmatic cluster randomised trial comparing the implementation of the six recommendations using tailored interventions with no intervention [29].

We will randomise 80 municipalities into one of two groups: an intervention group, to which we will deliver tailored interventions to implement the six recommendations, and a control group, to which we will not deliver any intervention. We will randomise municipalities rather than patients, individual clinicians or practices because we will deliver the intervention for the first three recommendations at the municipal level and we want to minimise the risk of contamination across practices for the other three recommendations.

The flow of participants through the trial is shown in Figure 1. All 80 selected municipalities will be randomised at the start of the study. The tailored intervention will be delivered over six months, beginning in October 2013 and ending in March 2014.

**Figure 1 F1:**
[figure not shown]
**Flowchart for the randomised controlled trial.** RCT, randomised controlled trial.

### Participants and settings

We will include 80 municipalities. We have selected municipalities from these counties: Aust-Agder, Vest-Agder, Akershus, Oslo, Hedmark, Oppland and Troms (see Additional file 1: Appendix C for details of each municipality). The municipalities within these counties have been selected for pragmatic reasons (geographical access by the research team) and because they represent both urban and non-urban communities and large and small municipalities in Norway, and hence they are representative of the municipalities in Norway.

At the health-care professional level, we will include GPs in the data collection. Although the resources provided apply to and will be aimed at all health-care professionals in the municipalities (including specialists in private practice), we will mainly target our interventions at GPs because the GP practice is a core service for most elderly patients, and our primary outcome is measured at the GP level.

At the patient level, we will include elderly patients who live at home, 65 years or older, with a diagnosis of mild, moderate, severe or recurrent depression or assumed to have a diagnosis of depression according to standardised criteria (see Additional file 1: Appendix A) and who have consulted their practitioner within the last six months before the intervention.

### Eligibility criteria

All practising GPs in the included municipalities are eligible. Eligible patients will be identified by extracting information from GPs’ electronic medical records, using an algorithm based on the diagnostic codes in the International Classification of Primary Care, 2nd edition (ICPC-2). It is mandatory for Norwegian GPs to use this classification system in their contact with patients. Furthermore, the algorithm will contain ICPC2 diagnostic text, free text, prescription of antidepressants and billing codes. We will use several criteria to identify depressed elderly patients, even if they do not have a recorded diagnosis of depression, because many practitioners will use other diagnostic codes. The algorithm will give a score from one to six, the lower score indicating a lower probability that the patient is suffering from depression. A definite diagnosis and assessment of the severity of a patient’s depression will be based on the International Statistical Classification of Disease and Related Health Problems (ICD-10) [30] (in order to distinguish each case with regard to depression severity (mild, moderate or severe) and whether the patient suffers from recurrent or chronic depression or dysthymia. Patients will be excluded if they have a diagnosis of dementia, bipolar disorder or reside in nursing homes or are assessed by their practitioner to have low life expectancy.

From each GPs’ list we will choose a total of six patients with depression. Each list will be sorted using the score from the algorithm. We will choose patients from the top of the list. If a list contains more than six patients with a score of six, we will select from those patients randomly. If any of the first six patients identified do not suffer from depression according to the ICD-10 criteria, we will chose more patients from the list, until we have identified six patients with depression according to the ICD-10 criteria.

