### ICD-10 classification of depression

These criteria are to be used in interviews with GPs to identify eligible patients and to grade the severity of depression.

The severity of a depressive episode is:

• mild (F32.0): at least two typical symptoms, plus at least two other common symptoms; none of the symptoms intense

• moderate (F32.1): at least two typical symptoms, plus at least three other common symptoms; some symptoms marked

• severe (F32.2): all three typical symptoms, plus at least four other common symptoms; some symptoms severe with intensity

• severe with psychotic symptoms (F32.3); as described in F32.2 but with delusions, psychomotor retardation or stupor so severe that ordinary social activities are impossible

A recurrent depressive disorder (F33) is where there are recurrent depressive episodes. Persistent mood disorders (F34.1) are known as dysthymia. An abridged depressive episode has a minimum duration of episode of about two weeks.

Typical symptoms (the core symptoms) are: depressed mood, loss of interest and enjoyment, reduced energy and increased fatigability.

Other common symptoms are: reduced concentration and attention, reduced self-esteem and self-confidence, ideas of guilt and unworthiness, agitation or retardation, ideas or acts of self-harm or suicide, disturbed sleep and diminished appetite.

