#### Secondary outcomes

We will measure the following patient outcomes for up to six patients for each GP. Most of these outcomes will be assessed by the patients themselves.

1. Global improvement in depression as assessed by the GP using the Clinical Global Impression Scale – Improvement (CGI-I) [31].

2. Improvement in depression as assessed by the patient or a family member:

• Patient Global Impression – Improvement (PGI) [32,33]. CGI-I and PGI are identical measures, using a 7-point Likert scale, where 1 means very much improved, and 7 is very much deteriorated.

• The presence of symptoms of depression and/or anxiety using the Hospital Anxiety and Depression Scale (HADS) [34]. HADS is a 14-item questionnaire, of which seven items measure depressive symptoms and seven items measure anxiety.

3. Loneliness [35,36]

• Do you sometimes experience loneliness? (0 = often, 1 = sometimes, 2 = seldom 3 = never)

4. Social contact

• Did you lack social contact when you first discussed being depressed with your GP? (yes/no)

• If yes, did you subsequently establish social contact with the help of a voluntary organisation or by other means? (0 = no, 1 = once only, 2 = more than once)

5. Physical activity

• Were you physically inactive when you first discussed being depressed with your GP? (yes/no)

• If yes, have you subsequently become more physically active? (yes/no)

6. Sleep problems

• Did you have a problem sleeping when you first discussed being depressed with your GP? (yes/no)

• If yes, has the sleeping problem improved?^b^

7. Anxiety

• Did you have a problem with anxiety when you first discussed being depressed with your GP? (yes/no)

• If yes, has your ability to cope with your anxiety improved?^b^

8. Problem-solving

• Did you have difficulties with problem-solving when you first discussed being depressed with your GP?

• If yes, has your ability to solve problems improved?^b^

9. Use of a self-help programme or reading self-help literature

• Have you used a self-help programme or read self-help literature? (yes/no)

10. Adherence with antidepressants

• Self-reported measure of medication adherence [37,38]

1. Do you ever forget to take your medication?

2. Are you careless at times about taking your medicine?

3. When you feel better, do you sometimes stop taking your medicine?

4. Sometimes when you feel worse, do you stop taking your medicine?

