### Data collection

At the start of the study we collected the following baseline data for each municipality:

• Number of inhabitants, number of elderly patients (65+), the proportion of inhabitants aged over 80 and the number of GPs (from Statistics Norway and the municipalities)

• Whether the municipality has collaborative care plans for elderly patients with depression, for adult patients with depression, or for adults with mental health problems including for elderly patients with depression (collected by questionnaire with telephone follow-up if needed). If so, we will obtain a copy for further analysis

• Written agreements for routines for referral within primary care and between primary care and specialist health care

• A plan for depression care managers

• A plan for collaboration with voluntary organisations

• Whether the municipality is a member of the ‘Centre for Development of Institutional and Home Care Services’ network.

• Whether the primary-care-based psychiatric nurse teams provide regular services to the elderly population (65+)

We will collect outcome data beginning three months after the delivery of the intervention. In both groups we will collect data for all eligible patients using GPs’ medical records, structured interviews with GPs, brief questionnaires mailed to patients and questionnaires mailed to each municipality (with telephone follow-up, if needed). We anticipate that treatment strategies provided to patients with depression may take up to three months to prove beneficial.

Prior to contact with GPs, we will send them a program that will extract and identify eligible patients from their medical records. We will contact each GP practice that has consented to participate by telephone and identify eligible patients in their electronic medical records using the algorithm described in Additional file 1: Appendix A and collect the following information using structured telephone interviews with each GP:

• Depression severity according to ICD-10 for six patients identified with depression

• GP’s adherence to recommendations (primary outcome measure)

• GP’s assessment of a patient’s improvement, as measured CGI-I (secondary outcome measure)

• GP’s awareness and knowledge of a collaborative care plan in the municipality

If the GP faces any technical problems using the electronic device, we will provide support to solve the problem and if needed visit the GP to collect data.

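### ICD-10 eligibility and severity are judged in interviews after the intervention with no reference date, so recovery can decide who is sampled and how care is scored

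*Protocol article*

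**What the plan says.** All references are to the protocol article.

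- **Who qualifies.** Participants and settings includes home-dwelling patients aged 65 or over with diagnosed or assumed depression "who have consulted their practitioner within the last six months before the intervention".
- **When the intervention runs.** Trial design: "The tailored intervention will be delivered over six months, beginning in October 2013 and ending in March 2014".
- **Where the ICD-10 criteria are applied.** ICD-10 classification of depression: "These criteria are to be used in interviews with GPs to identify eligible patients and to grade the severity of depression".
- **When those interviews happen.** Data collection: "We will collect outcome data beginning three months after the delivery of the intervention". Severity, adherence and the GP's CGI-I rating are all collected in the same structured telephone interview.
- **What happens to patients who fail the check.** Eligibility criteria: "If any of the first six patients identified do not suffer from depression according to the ICD-10 criteria, we will chose more patients" from the GP's list, until six with ICD-10 depression are found.
- **What the grade does.** Under Primary outcome, severity selects the questions: seven for mild, seven for moderate, two for severe.
- **What is measured on patients.** Secondary outcomes begins with "Global improvement in depression as assessed by the GP using the Clinical Global Impression Scale", followed by PGI and HADS.
- **Blinding.** The Blinding section says that participants and researchers cannot be blinded to the intervention.

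**The concern.** The population is defined before the intervention, but membership is settled after it, by a check with no stated reference date. If the GP answers for the day of the interview, a patient who was depressed at the qualifying consultation and has since recovered fails the check and is replaced. Inclusion then depends on what CGI-I, PGI and HADS are meant to measure. If the intervention speeds recovery, more patients are removed in its arm than in the control arm.

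The grade raises a second problem. Severity decides which recommendations count for a patient. If it is the severity at interview, the care is compared with recommendations for a state the patient may not have been in when treated, and one that the intervention may itself have changed.

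Both are rules of sampling and measurement. Once a patient has been replaced, no later analysis can bring that patient back.

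**Working it through.** **Plan's own figures.** The article gives no power or sample size for patient improvement. Its sample counts reproduce: 80 × 10.93 × 0.5 = 437 GPs, and 437 × 6 = 2,622 patients at most. Those patient places are what the replacement rule fills. The stated power of 0.80 concerns adherence and does not bear on this point.

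**Step 1: the interval.** Delivery starts in October 2013, so the qualifying window is April to September 2013. Delivery ends in March 2014; adding three months gives interviews from about July 2014. From the end of September 2013 to July 2014 is 9 months, and from the start of April 2013 it is 15 months. The check is made at least 9 to 15 months after the consultation.

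**Step 2: patient outcomes if current status is used (all inputs assumed).** Let recovered patients score 1.5 on CGI-I (1 = very much improved) and unrecovered controls 3.5. Let recovery be r in the control arm and r + 0.10 in the intervention arm, with r = 0.20, 0.30 or 0.40. Let m be the mean for unrecovered intervention patients.

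Difference in all patients = [1.5r + 3.5(1 − r)] − [1.5(r + 0.10) + m(0.90 − r)]

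Difference after replacement = 3.5 − m

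| m | All patients, r = 0.20 / 0.30 / 0.40 | After replacement | Share kept |
|---|---|---|---|
| 3.5 (benefit through recovery only) | 0.20 / 0.20 / 0.20 | 0 | 0% |
| 3.2 | 0.41 / 0.38 / 0.35 | 0.30 | 73 to 86% |
| 3.0 | 0.55 / 0.50 / 0.45 | 0.50 | 91 to 111% |

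Example for r = 0.20, m = 3.2: (0.30 + 2.80) − (0.45 + 2.24) = 0.41. Replacement can erase, shrink or barely alter the contrast, depending on how the benefit arises.

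**Step 3: mean adherence through selection alone (inputs assumed).** Let a patient's share of items delivered have mean μ (0.40 control, 0.45 intervention) and SD s. Let the probability of recovery be b + L × share, with b = 0.3 or 0.5 and L = 0.2 or 0.4. The mean among unrecovered patients is

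μ − L s² / (1 − b − Lμ).

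- b = 0.3, L = 0.2, s = 0.17: 0.05 − 0.2 × 0.0289 × (1/0.61 − 1/0.62) = 0.0498.
- b = 0.5, L = 0.4, s = 0.30: 0.05 − 0.4 × 0.09 × (1/0.32 − 1/0.34) = 0.0434.

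A simulation of 2 million patients per arm, with seven items and beta-distributed patient adherence, gave 0.0486, 0.0481, 0.0454 and 0.0412 over the same four pairs of b and L. The true difference is 0.050 throughout.

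**Step 4: the item set.** This is not part of Step 3.

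- *Severe when treated, mild at interview.* The patient was referred to a case manager, prescribed antidepressants and offered psychotherapy, with no self-help programme and no counselling topic discussed. On the severe set this is 2/2. On the mild set, referral and psychotherapy are not asked about, and the antidepressant counts against the GP unless the previous-response exception applies: 0/7 or 1/7. If the GP mean averages six patient proportions equally (assumed), a change from 1 to 0 in one patient moves it by 1/6 = 0.17.
- *Moderate when treated, mild at interview.* Six of the seven questions are the same. The case-manager question is replaced by the antidepressant question, so at most 1/7 = 0.14 of that patient's score is affected.

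These are shifts in level. They reach the contrast between arms only so far as changes in severity, or the care given, differ by arm. The documents give no figure for that, and the direction is not determined.

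**The case against.** The strongest reply is that the authors meant the episode for which the patient was treated. Much of the article fits that. The population is tied to a pre-intervention consultation. The search deliberately takes in patients without a recorded diagnosis, so replacement may serve only to remove its false positives. The patient questions look back to the first discussion of depression with the GP. CGI-I and PGI run up to very much improved. Data collection waits three months so that treatment can show benefit, which sits poorly with discarding those who benefit. Recurrent depression and dysthymia are eligible and need not depend on a current episode. Appendices A and E of the additional file, which hold the standardised criteria and the schedule, are not at hand and may fix the date.

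This stands as evidence of intent, and it rules out three stronger readings that a reader might infer:

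- **That recovered patients are excluded by rule.** No section says so. It follows only if the check concerns the day of the interview.
- **That the trial cannot show patient improvement.** Even on the current-status reading, partial improvement among patients still depressed registers on CGI-I, PGI and HADS (Step 2). Patient improvement is also a secondary outcome.
- **That about 70% of episodes would have ended by interview.** The Background says "The risk that an elderly patient with depression develops a chronic episode is estimated to be approximately 30" per cent. The complement of a chronic-course risk with no stated duration is not a recovery rate at 9 to 15 months, and the same section says that episodes in the elderly are longer.

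The reply does not settle the point. The qualifying window dates the consultation, and the look-back items belong to the patient questionnaire. Neither says when the ICD-10 criteria must be met. The operative sentence is in the present tense, so interviewers and GPs could apply either reading.

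**Conclusion.** The point holds as a defect in a stated rule. Eligibility and severity are judged after the intervention by unblinded GPs, non-cases are replaced, and no reference date is fixed. Applied as worded, this permits selection that depends on outcome and may differ by arm.

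- **Patient outcomes.** A benefit acting only through recovery would vanish from CGI-I, PGI and HADS. A broader benefit may be reduced or little changed. This rests on the current-status reading and on the assumed scores in Step 2.
- **Primary outcome, selection.** Probably small: 0.041 to 0.049 against 0.050, with recovery parameters that no document supplies.
- **Primary outcome, scoring.** A single patient's score can change from 2/2 to 0/7 through the grade alone. The net effect on the difference between arms cannot be sized from the article.

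How many patients would be replaced is unknown, and no recalculation of sample size follows.

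**What to change.** Change three places: Eligibility criteria, ICD-10 classification of depression, and Data collection.

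1. State that the ICD-10 diagnosis and severity grade refer to the patient's episode at the qualifying pre-intervention consultation, taken from the medical record that the GP has available during the interview.
2. Replace a patient only if the criteria were not met then, and keep patients who have since recovered.
3. Score adherence on the item set for that reference severity.

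The state at follow-up is then recorded through CGI-I, PGI and HADS alone.

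The cost is a few sentences in the protocol and the interview script, with no extra patients or contacts. There are two downsides. Unblinded GPs would grade severity retrospectively over 9 months or more, which is somewhat less certain than a current rating. Later changes in severity would also not alter the item set.
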